### Data collection software application

Currently, the DHS and Multiple Indicator Cluster Survey (MICS) surveys are administered either using a paper version of the questionnaire (PAPI) or computer assisted personal interviewing (CAPI) and the CSPro (Census and Survey Processing System) platform for entering the data entry or data capture. We elected to use Android-based tablet data collection as most of the selected HDSS sites had some experience with these. We compared several existing data collection platforms (ODK, CSPro, Qualtrics, Red Hat and Survey Solutions). We selected the Survey Solutions Computer Assisted Personal Interview and Computer Assisted Web Interviewing platform (Survey Solutions) developed by the World Bank [32], given its ability of linking questions to specific household members listed in the roster file; its flexible and user-friendly online interface for the questionnaire design; the ability to integrate validation rules; lack of user fees; the online tool for centralised survey administration and data management; data aggregation and reporting features; end-user technical support provided by the World Bank technical support team; as well as the Interviewer application available for Android devices.

The data will be entered on Android-based tablets using the Survey Solution platform, stored locally on the tablets, and synchronised regularly to the dedicated country’s physical or virtual server. The platform has different user roles with varying level of permissions and functions: Interviewer (function – data collection), Supervisor (assigning and monitoring data collection by interviewers), Headquarters (overall survey and data management), and Observer (monitoring) (**Figure 4**). The platform’s survey and data management component (‘Survey Solutions Headquarters’, HQ) provides a dashboard of the progress of data collection, including duration and speed of the interviews, Global Positioning System coordinates of the interviewer, as well as paradata. The paradata contains information about the process of collecting survey data and records all events with timestamps on a tablet during data collection (data entry, data correction, responsibility changes, etc.). This type of data can be used for analysis of time per interview and time per question and section, as well as changes in productivity over time for different interviewers and teams. These data can be used for live data quality control, data monitoring and interview progress evaluation.

**Figure 4 F4:**
[figure not shown]
EN-INDEPTH Data Collection and Flow.

### Procedures

#### Informed consent and respondent identification

All participants will receive a verbal explanation of the study objective by a trained field assistant and an information sheet. An adapted version of the standard DHS consent form will be used (Appendix S4 in **Online Supplementary Document**). Both will be translated into local languages and written consent will be obtained from all study participants. Study participants will be informed of their right to refuse and/or withdraw at any point of time from the survey interviews, and at liberty to answer those questions they want to and will not be coerced in case they refuse. Information obtained will be viewed only by the researchers and anonymity will be guaranteed by using identification numbers. Separate written consent will be sought for women and interviewers participating in the qualitative aspects. We will follow fieldwork procedure as outlined in the DHS interviewer manual. Interviewers will make up to three attempts to find respondents.

### Randomisation and EN-INDEPTH survey

Women selected for the survey from all five sites will be randomised to receive either the reproduction questions from the DHS-7 women’s questionnaire with a standard FBH^+^ or a FPH. Randomisation will be done automatically within the application-based questionnaire using an in-built random number generator.

**Table 4** provides a summary of adaptations to the DHS-7 questionnaire sections to meet the study objectives including questions on gestational age, birth certification, characteristics of stillbirths and fertility intentions. The latest DHS questionnaire (DHS-7) will be used, with a shortened introduction section 1 of the DHS-7 women’s questionnaire; section 2 on reproduction; section 4 on pregnancy, delivery and postnatal care; and an additional section 9 adapted on household characteristics. Section 8 on fertility intentions was optional and the Matlab site opted not to administer this as they have just recently completed the collection of similar data. Some specific country add-on modifications will be made to the questionnaire (eg, Bandim site will collect questions on vaccinations, and the IgangaMayuge site will collect data using the Dietary Diversity questionnaire in section 10). Apart from section 2, the questionnaires for the FBH^+^ and FPH arms will be identical. Section 2 in the FBH^+^ arm will contain the standard DHS-7 core reproduction questions. In the FPH arm, section 2 will contain the whole reproduction section from the Nepal 2016 DHS for sites willing to include detailed questions on abortion, and a reduced version without the detailed abortion questions for other sites. Appendix S5 in **Online Supplementary Document** gives full details of the questionnaires.

**Table 4 T4:** Current standard DHS Phase 7 questionnaire sections and adaptations for this study

Survey questionnaire with FBH^+^ or FPH detailing adaptations from standard DHS phase 7 section, where applicable	
**Section 1. Consent form and background of interview**	The content of section 1 will be reduced to focus on key maternal background characteristics only.
**Section 2. Reproduction**	Standard FBH^+^ questions with pregnancy loss questions which include information on stillbirths, miscarriages and abortions. No adaptations made. Or randomly allocated to FPH from Nepal 2016 for the FPH and pregnancy losses questions – the detailed questions on abortion will only be administered in selected sites.
**Section 4. Pregnancy and postnatal care**	Section 4 will be administered with minor adaptations for all stillbirths and neonatal deaths, as well as for a sample of live births. Additional questions on gestational age (weeks), birth and death certification, and timing and characteristics of stillbirths will be added to test the feasibility of these questions in household surveys.
**Section 8. Fertility preferences**	Some questions on fertility intention to refine the measurement on unwanted pregnancy will be added. These questions have been developed and tested in a multi-country research study [33].
**Section 9. Household characteristics**	Questions on household socio-economic characteristics including household dwelling structure, flooring material, sanitation and toilet facility. These questions are adapted from the DHS household survey questionnaire.

FBH^+^ – full birth history +; FPH – full pregnancy history; DHS – Demographic and Health Surveys.

Local language translations of the questions already used by DHS will be used whenever available. Where not available, translations to local languages will be made by the site teams and checked using back translation.

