## METHODS

### Study design

This multi-site study will use a retrospective survey to compare two methods of recording pregnancy outcomes (FBH^+^ vs FPH methods), with random allocation at the individual woman level. Quantitative and qualitative data will be collected to answer four research objectives (**Table 1**).

Research protocol development was informed by wide consultation, including review by the research site teams and an Expert Advisory Group. 23 participants took part in a study design workshop in Kampala in mid-2016 [28]. In addition, in April 2017, a multi-site workshop was organised to agree on the data collection protocol in the five sites.

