**Sampling frame***	Women in HDSS site with recorded birth outcome in last 5 y. (all in urban site and 80% in rural site)	Women in HDSS site with recorded birth outcome in last 5 y. (all)	Women in HDSS site with recorded birth outcome in last 5 y. (random sample)	Women of reproductive age in HDSS site	Women of reproductive age in HDSS site	
**Expected number of total births to be captured in survey**	17 000	21 000	14 500	5700	9800	68 000

HDSS – Health and Demographic Surveillance Systems

*See Appendix S3 in **Online Supplementary Document** for details.

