#### Data quality monitoring

Validations for value ranges were defined and programmed into the tablet application to avert predictable human errors. The skipping rules were programmed and additional rules were set to perform consistency checks. Warning messages were programmed to prompt to correct the input when values are outside the defined range, and to provide guidance as per the DHS manual. Data quality will be monitored using Survey Solutions platform’s online data dashboard, providing real-time cumulative and detailed summary of ongoing surveys across teams and individual interviewers in each country. The platform allows Supervisors and Headquarters to validate collected data by Interviewer online and, if necessary, incomplete or erroneous questionnaires can be returned to the Interviewer for timely re-assignment and correction. In addition, bi-weekly reports will be sent to the LSHTM and MakSPH core teams by data analysts from all sites summarising the overall data collection progress. Regular all-site data monitoring calls will provide an opportunity for country teams to review and discuss progress in addition to promoting collaborative quality improvement initiatives between countries and sites.

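### The FBH+/FPH arm is drawn inside the interviewer's tablet questionnaire, and nothing stated ties a woman's first draw to her, so selective redraws are not ruled out

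*Protocol article*

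**What the plan says.** The Study design section describes a comparison "with random allocation at the individual woman level". The section on randomisation and the survey repeats the unit, "Women selected for the survey from all five sites will be randomised to receive either the reproduction questions", and then gives the mechanism: "Randomisation will be done automatically within the application-based questionnaire using an in-built random number generator".

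Other statements bear on how that mechanism works in the field:

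- **Frame.** In Table 2 the frame for Bandim, Matlab and Kintampo is "Women in HDSS site with recorded birth outcome in last 5 y". Dabat and IgangaMayuge take all women of reproductive age in the site.
- **Order of the questionnaire.** Table 4 puts consent and background in Section 1 and the arm-specific module in Section 2 of the same instrument.
- **Contact.** "Interviewers will make up to three attempts to find respondents".
- **Corrections.** Under Data quality monitoring, "incomplete or erroneous questionnaires can be returned to the Interviewer for timely re-assignment and correction".
- **Audit trail.** The section on the data collection software says that the paradata "records all events with timestamps on a tablet during data collection".
- **Length.** The introduction says that FPH may take longer, and the Discussion treats this as a question for the study to answer.

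The article does not say whether the draw is stored against the woman's identifier, whether a second questionnaire can be started for her, or which arm would count if one were.

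**The concern.** The unit to be randomised is a woman, but the stated draw is made within a questionnaire. Unless the two are bound together, the arm belongs to a record and not to a person. The person who operates the record learns the arm at Section 2 and may have a reason to prefer the shorter module.

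Women with long or difficult histories plausibly include more women with losses, and their FPH interviews are plausibly the ones most often broken off. That is an inference; the article does not report it. If some of those women were started again and landed in FBH+, stillbirths would leave the FPH arm and enter the FBH+ arm. The ratio would shrink towards or below the 15% difference that the sample size section treats as the smallest that would justify changing the DHS questionnaire. The study has only about 80% power at that difference, so it has little room for such dilution.

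**Working it through.** **1. Reproduce the planned figure.** Inputs from the sample size section and the highlighted row of Table 3: stillbirth rates of 23.2 (FBH+) and 26.7 (FPH) per 1000 total births, alpha 0.05, power 80%, design effect 1.1, at least 68 000 births. Two-proportion formula, pooled variance, two-sided, 1:1, no continuity correction:

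- Total births = 62 348, as in Table 3.
- 62 348 × 1.1 = 68 583, as in Table 3.
- Power with 68 000 / 1.1 births = 79.7%; ratio 26.7 / 23.2 = 1.151.

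No planned figure is wrong. The documents give no switching rate, so everything below rests on assumed values.

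**2. Switching unrelated to outcome.** Let a share s of FPH draws get one fresh 50:50 draw. The FPH share becomes 0.50 − 0.25s, the rates do not change, and only the balance of the arms suffers.

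| s | FPH share | Power |
|---|---|---|
| 0 | 50% | 79.7% |
| 10% | 47.5% | 79.6% |
| 20% | 45% | 79.4% |

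**3. Selective switching.** Let a fraction f of FPH-drawn women end up in FBH+, with k times the average stillbirth risk:

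- FBH+ rate = 23.2 × (1 + fk) / (1 + f)
- FPH rate = 26.7 × (1 − fk) / (1 − f)
- Births per arm = 34 000 × (1 ± f) / 1.1

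Worked case, f = 2%, k = 2: FBH+ = 23.2 × 1.04 / 1.02 = 23.65; FPH = 26.7 × 0.96 / 0.98 = 26.16; ratio 1.106; power 51%.

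| f | k | Ratio | Power |
|---|---|---|---|
| 0 | – | 1.151 | 79.7% |
| any | 1 | 1.151 | almost unchanged for small f |
| 0.5% | 1.5 | 1.145 | 77% |
| 1% | 1.25 | 1.145 | 77% |
| 1% | 2 | 1.128 | 67% |
| 2% | 1.5 | 1.128 | 67% |
| 2% | 2 | 1.106 | 51% |
| 3% | 2 | 1.084 | 36% |

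Here f counts women who actually finish in the other arm. If each redraw is 50:50, about 2f of FPH interviews must be restarted: about 1%, 2%, 4% and 6% for f = 0.5%, 1%, 2% and 3%.

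**4. A second model for direction.** Suppose that only births reported as stillbirths under FPH are redrawn, with probability s, and that moved cases are then reported at the FBH+ rate. With m = s/2, and rates as proportions, FPH = 0.0267(1 − m) / (1 − 0.0267m) and FBH+ = 0.0232(1 + m) / (1 + 0.0267m). The ratio is 1.096 at s = 5%, 1.044 at 10% and 1.004 at 14%. Redrawing about one in seven such cases would erase the planned difference. This is the extreme form of selection and shows direction, not a forecast.

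**The case against.** The strongest reply is that the documents do not show a redraw happening. Three stronger readings are tempting, and none is supported.

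- **That a reopened questionnaire gets a fresh draw.** The article does not say so. A saved record may well keep its draw, and sending a record back for correction suggests that its content is kept. The three attempts concern finding a woman, not restarting an interview that has reached Section 2. The only plausible route is a second questionnaire started for the same woman, and the article is silent on whether the application permits one.
- **That switching could not be detected.** Tablet events are time-stamped, supervisors assign and monitor the work, and survey records are to be matched individually to HDSS data. Any of these could expose two records for one woman. What stands is that the article plans the paradata for timing and quality control and commits to no check on allocation; detection would also come after the event.
- **That the plan expects FPH to be slower.** It says only that it may be.

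Two further replies carry some weight. Storage of the random number and blocking of duplicates may be covered in the set-up, listing and application manuals or in Appendix S5, which are not shown. But the article itself chose to fix the mechanism, and a safer one is available, so this is more than a detail left to another document. An automatic draw also leaves no advance list for interviewers to read, which protects concealment. A preloaded arm gives up that protection unless the field stays hidden until consent and Section 1 are complete.

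**Conclusion.** The concern holds as an exposure, not as a demonstrated bias. The stated mechanism puts the draw in a tool run by someone who then sees the arm, and nothing stated binds the first draw to the woman.

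The size depends wholly on two assumed quantities. With no selection (k = 1) there is no bias and almost no loss of power. With mild selection (f = 0.5%, k = 1.5) the ratio is 1.145 and power 77%, which is minor. With f = 1% to 2% and k = 2 the ratio is 1.13 to 1.11 and power 67% to 51%, enough to turn a true 15% difference into a likely null result. Those last cases need roughly 2% to 4% of FPH interviews to be restarted, in women at twice the average risk. A reader should not infer that this is the expected rate. The sample size itself is unaffected.

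**What to change.** Before fieldwork, allocate every listed woman 1:1 within site against her HDSS identifier. Preload the arm as a hidden, read-only field that the application reveals only after consent and Section 1, so that any returned, re-assigned or newly started questionnaire for that identifier carries the same arm. Keep an in-app draw only for eligible women who are not on the list.

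If preloading is not possible at a site, lock and log the first draw per identifier.

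In either case, state that the comparison is analysed by first allocation, and tabulate the arm split, break-offs and duplicate records by interviewer and site during data collection.

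The cost is one allocation file per site, one extra field in the questionnaire, and care to keep that field concealed. No additional women, births or visits are needed.

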#### Assessment of barriers and enablers to reporting of pregnancy and adverse pregnancy outcomes

For objective 4, a self-administered questionnaire adapted from DHS fieldworker questionnaire, will assess demographic and other characteristics of the interviewers (Appendix S6 in **Online Supplementary Document**). A series of Focus Group Discussions (FGDs) will be held with HDSS and survey interviewers, as well as supervisors, to assess the barriers or enablers to collecting data on pregnancy and adverse pregnancy outcomes in the survey and HDSS. FGDs will be conducted with women who had at least one pregnancy in the past five years, focusing on perceptions, practices, barriers and enablers in the community. A minimum of six FGDs will be conducted in each site, each with approximately eight to ten participants. In-Depth Interviews (IDIs) will be undertaken in some sites with women who have experienced these adverse pregnancy outcomes, allowing for deeper exploration and triangulation of data.

#### Training of data collectors and supervisors

The EN-INDEPTH site teams with LSHTM and MakSPH jointly developed a training manual on the data collection procedures, adapting the standard DHS Interviewer’s Manual [34], and tailored it to the specific country context and the HDSS site. Four additional manuals (data collection setup, Survey Solutions data management procedures, listing process, Survey Solutions Tester/Interviewer application) were developed adapting the World Bank Survey Solutions Manuals [35]. The training of data collectors and supervisors was led by the HDSS team with initial support from the core team for a minimum of two weeks in all HDSS sites. The training included at least one-week on the paper-based questionnaire and one to two weeks on tablet use, data collection using the Survey Solutions Tester application, as well as the Survey Solutions Interviewer application and interviewer field practice. Prior to data collection, additional trainings on survey management using Survey Solutions HQ were provided to supervisors and data analysists.

For the qualitative work, training manuals will be developed to guide the interviewers during the FGDs and IDIs to ensure comparability of interviews across sites. Additionally, a protocol will be developed to guide the interviewers on how to react in situations where the respondent gets distressed. After the initial two to three weeks training, all sites will initiate the pilot phase of data collection. The length of the data collection will vary by site depending on the fieldwork schedule and allocated sample size ranging between six to 12 months.

#### Data quality monitoring

Validations for value ranges were defined and programmed into the tablet application to avert predictable human errors. The skipping rules were programmed and additional rules were set to perform consistency checks. Warning messages were programmed to prompt to correct the input when values are outside the defined range, and to provide guidance as per the DHS manual. Data quality will be monitored using Survey Solutions platform’s online data dashboard, providing real-time cumulative and detailed summary of ongoing surveys across teams and individual interviewers in each country. The platform allows Supervisors and Headquarters to validate collected data by Interviewer online and, if necessary, incomplete or erroneous questionnaires can be returned to the Interviewer for timely re-assignment and correction. In addition, bi-weekly reports will be sent to the LSHTM and MakSPH core teams by data analysts from all sites summarising the overall data collection progress. Regular all-site data monitoring calls will provide an opportunity for country teams to review and discuss progress in addition to promoting collaborative quality improvement initiatives between countries and sites.

#### Data management

Following synchronisation, data from tablets will be uploaded to the country’s dedicated virtual or physical server with regular automatic back-up, with additional back-up on a separate server or external hard drive. The raw data will be stored in an encrypted format, accessed only by the country’s data manager. The anonymization of the quantitative and qualitative data (removing any direct or indirect identifiers, including enumeration identifiers, geo-referenced data, transcripts and audio recording) will take place in-country before data sets are pooled into one multi-site data set (**Figure 4**).

### Analysis by objective

The overview of research objectives, main research questions, and analytical approaches are summarised in **Table 1**. For all study objectives, the primarily analyses will be performed overall across countries (as pooled analyses), and comparative secondary analyses will be performed by site separately, whenever possible. Data will be cleaned according to an agreed protocol, including logical and completeness checks. Quantitative analyses will be undertaken with Stata 15SE (Stata Statistical Software: Release 15. College Station, TX: StataCorp LLC). Qualitative analyses will be conducted using NVivo software (NVivo qualitative data analysis Software; QSR International Pty Ltd Version 12, 2018).

#### Objective 1

A population-level descriptive analysis will be conducted comparing SBR and NMR by FBH^+^ or FPH, and by maternal characteristics (age, parity, residence, and education status). Crude risk ratios with its 95% confidence interval will be computed for comparison of SBR and NMR between FBH^+^ and FPH overall and by study site using the meta-analysis methods with Random Effects. Regression models will be fitted to assess determinants of adverse pregnancy outcomes using Generalised Estimation Equations to adjust for clustering of stillbirths or neonatal deaths within the same woman, therefore taking into account design effect. We will use paradata to assess differences in average time taken to complete the FBH^+^ and FPH.

#### Objective 2

We will undertake descriptive analyses of selected indicators including fertility intentions, selected pregnancy outcomes (TOP, miscarriage, birthweight, gestational age), as well as birth and death registration. This will include estimates of frequency of reported TOP and miscarriage, coverage of reported birthweight, gestational age, birth and death certification, and of fertility intentions. The answerability of new/refined questions will be assessed by describing patterns of non-response and heaping, where appropriate. Variation in these indicators by pregnancy outcome, maternal or interviewer characteristics will be assessed. For gestational age, internal consistency in the survey will be assessed by comparing women’s reporting of gestation in months compared to weeks, and reported maternal perception of the birth to be preterm. Survey paradata will also be analysed to assess time taken to complete and frequency of repeated corrections to relevant survey questions.

#### Objective 3

Women-level data from the survey will be individually matched with the routine HDSS surveillance data to establish matching rates for stillbirths and neonatal deaths. We will assess determinants of reporting or not reporting of these outcomes in the survey by women’s and interviewers’ characteristics and HDSS settings (geographic, socioeconomic, cultural, data collection methodologies, etc.). We will also assess levels of agreement between the survey and the routine HDSS data over the same time period at a population level for several indicators, such as SBR, NMR, miscarriage, TOP, birthweight, and gestational age. Predictors of disagreement (eg, length of recall, maternal education, etc.) will be examined. We recognize that neither HDSS nor survey data can be considered ‘gold standard’ and that the difference in measurement might be in both or either direction and variable by site.

#### Objective 4

For qualitative data, we will use a grounded theory approach for analysis, with an iterative process involving reading the text, detecting potential emerging themes and outliers, comparing themes and searching for relationships, as well as building theoretical models. A priori coding will be done, with a codebook listing potential codes developed before the analysis begins, to guide the process, and new codes identified from data included as analysis proceeds. Results will be presented with verbatim quotes from respondents. Reliability will be checked by multiple members of the team, two from each site, independently coding data.

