### Sample size and data collection approach

Limited evidence from previous descriptive studies discussed above suggests a difference in SBR from 3 to 35% between a FBH^+^ and a FPH method [19,20]. A difference of at least 15% between the two methods could be sufficient to consider a major change in the DHS core questionnaire. Since this is the first direct comparisons of the two methodologies, we powered the randomized comparison to capture a 15% difference assuming that a difference less than 15% will not justify a change in survey methodology (see Appendix S1 in **Online Supplementary Document**).

Based on the recorded SBR and total births per HDSS over the last three years, the overall SBR for the final sample of births captured in the survey is expected to be around 28.4 per 1000 total births, if all women are surveyed. However, we needed to account for possible outmigration, unavailability of women at any visit, or non-consent. After adjusting for these factors, we expect the SBR for the FPH arm to be around 26.7 per 1000 total births (see Appendix S3, Table S2.2 in **Online Supplementary Document** for details). Assuming a SBR of 26.7 per 1000 total births in the FPH arm, a total sample size of at least 68 000 births would be required across the five sites to have 80% power to detect a difference of 15% or more between the proportion of total births that are stillbirths in the FBH^+^ and the FPH at the 5% significance level (alpha = 0.05), including a small design effect (DEFF = 1.1), as stillbirths may be clustered in individual women. The lower the SBR captured in the FBH^+^ arm, the higher the sample size will be required to detect 15% difference between the two arms (see **Table 3**).

**Table 3 T3:** Required sample size by stillbirth rate (SBR) for the household survey randomised comparison, assuming alpha = 0.05 and an expected 15% difference in SBR*

Assumed SBR in birth history group/ 1000 total births	Predicted SBR in pregnancy history group/ 1000 total births	Number of total births to achieve 80% power	Sample size - number of births required including design effect and non-response (15%)
23.00	26.45	63 604	80 459
23.20	**26.70**	**62 348**	**68 583**
24.00	27.60	60 886	77 021
25.00	28.75	58 386	73 858
26.00	29.90	56 078	70 939
27.00	31.05	53 942	68 237
28.00	32.20	51 958	65 727

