*The Design effect (DEFF) is calculated as DEFF = 1 + (r – 1) × rho, where r = average number of observations in a cluster and rho = correlation between pairs of observations selected at random from the same cluster). Assuming in a 5-year period women will experience on average a maximum of 2 births, and that as stillbirth is a rare outcome rho<0.1, a design effect of 1.1 is included. For Bandim, due to the challenge of reaching women in rural area, we can only account for a maximum of two visits to reach the interview, for this reason we have assumed a higher rate of non-response rate (30%).

For each site the approach to reach the maximum number of births was agreed based on site-specific information on the level of migration, geographical accessibility, and assumed levels of non-response (either due to non-consent or inability to locate) and other factors. The numbers per site are shown in **Table 2**and details of the estimation are in Appendix S3, Table S2.2 in **Online Supplementary Document**. Three sites (ie, Matlab, Dabat and IgangaMayuge) will survey all women who have given birth in the last five years. Matlab has bi-monthly data collection with pregnancy testing for women who report having missed a menstrual period, and hence has reliable listings of total births, and will administer the EN-INDEPTH survey to eligible women (age 15-49) known to have had at least one birth (live birth or stillbirth) in the last five years; Dabat and IgangaMayuge have bi-annual updates and do not have a specific system of pregnancy tracking and therefore, all women of reproductive age (15-49 years) in the HDSS site will be included. Bandim and Kintampo, will select a random sample of women residing in the HDSS known to have at least one birth in the last five years (**Table 2**).

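### The randomised comparison is specified as a crude per-birth risk ratio although women are randomised; the planned clustering adjustment is attached only to the models of determinants

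*Protocol article*

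**What the plan says.** All references are to the Protocol article.

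- **Unit of randomisation** (Study design): the comparison is made "with random allocation at the individual woman level".
- **Unit of outcome** (Sample size and data collection approach): the powered contrast is between "the proportion of total births that are stillbirths in the FBH^+^ and the FPH" arms, so the denominator is births.
- **Clustering in the sample size** (same section): the total is calculated "including a small design effect (DEFF = 1.1), as stillbirths may be clustered in individual women". The Table 3 footnote gives DEFF = 1 + (r – 1) × rho, with the inputs "Assuming in a 5-year period women will experience on average a maximum of 2 births" and rho below 0.1.
- **Analysis of the randomised contrast** (Analysis by objective, Objective 1): "Crude risk ratios with its 95% confidence interval will be computed for comparison of SBR and NMR between" the two questionnaire methods. The article goes on to say that this is done for each site and for all sites together, with random-effects pooling.
- **Clustering in the analysis** (next sentence of the same paragraph): "Regression models will be fitted to assess determinants of adverse pregnancy outcomes using Generalised Estimation Equations to adjust for clustering" within a woman, with the remark that the design effect is thereby accounted for.

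For this question Table 1 lists only descriptive and bivariate analyses, including meta-analysis. The opening of Analysis by objective makes the pooled analyses primary and the site-by-site analyses secondary.

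**The concern.** The authors accept that two births to one woman are not independent, and they enlarge the study because of it. The estimator named for the randomised question is nevertheless a crude ratio of birth-level risks. The method that would respect the woman as the unit is named one sentence later, for a different question. A programmer following the text would compute the ordinary interval for the ratio of two independent proportions, at each site and for both SBR and NMR.

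What is at stake is interval width and error rate; the point estimate is unaffected. Intervals would be too narrow at site level. The site variances passed to the meta-analysis would be too small, so some within-woman clustering would show up as differences between sites. The comparison is meant to inform whether the DHS core questionnaire should change, so its intervals should be valid for the design.

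**Working it through.** **1. Reproduce the plan's sample size.** Inputs from Table 3 and the text: p1 = 0.0232 (FBH+), p2 = 0.0267 (FPH), alpha 0.05, power 80%. Two-sided testing and 1:1 allocation are assumed; neither is stated, but together they reproduce the table.

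n per arm = [1.96 √(2 p̄(1 – p̄)) + 0.8416 √(p1(1 – p1) + p2(1 – p2))]² / (p2 – p1)², with p̄ = 0.02495.

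This gives 31 174 per arm and 62 348 in total, exactly as printed. Multiplying by 1.1 gives 68 582.8, the printed 68 583. The design effect is therefore fully in the sample size.

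**2. Range of the design effect.** DEFF = 1 + (r – 1) × rho.

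- The plan's ceiling is r = 2, rho = 0.1: DEFF = 1.10.
- Lower values are my assumption. With r = 1.2, rho = 0.02: DEFF = 1 + 0.2 × 0.02 = 1.004. With r = 2, rho = 0.05 (or r = 1.5, rho = 0.1): DEFF = 1.05.

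**3. Effect on a crude interval.** If the true variance is DEFF times the crude one, the crude standard error is 1/√DEFF of the correct one, and the two-sided type I error is 2 × [1 – Φ(1.96/√DEFF)].

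| DEFF | crude SE / correct SE | correct interval / crude interval | type I error |
|---|---|---|---|
| 1.004 | 0.998 | 1.002 | 5.05% |
| 1.05 | 0.976 | 1.025 | 5.6% |
| 1.10 | 0.953 | 1.049 | 6.2% |

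These figures apply to a site-specific comparison, to a simple pooled table, or to fixed-effect pooling.

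**4. The planned effect.** Take 34 000 births per arm (68 000 split 1:1) and risks of 26.7 and 23.2 per 1000. RR = 0.0267/0.0232 = 1.151, log RR = 0.1405.

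Crude SE = √[(1 – 0.0232)/(34 000 × 0.0232) + (1 – 0.0267)/(34 000 × 0.0267)] = 0.0481. Times √1.1 this is 0.0504.

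- Crude 95% interval: exp(0.1405 ± 1.96 × 0.0481) = 1.047 to 1.265.
- Interval at DEFF 1.1: exp(0.1405 ± 1.96 × 0.0504) = 1.043 to 1.270.

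**5. Effect on the random-effects result.** With five sites and no true heterogeneity, Cochran's Q should average 5 – 1 = 4. If each site variance is understated by a factor of 1.1, it averages 4 × 1.1 = 4.4, so heterogeneity is overstated. The extra between-site variance widens the pooled interval.

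I simulated DerSimonian-Laird pooling (an assumed estimator; the article names none) with the site sizes of Table 2 (17 000, 21 000, 14 500, 5700, 9800 births), 1:1 allocation, SBR 26.7 per 1000, no arm effect, no true heterogeneity, and one million replicates:

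| DEFF ignored | fixed-effect type I error | random-effects type I error |
|---|---|---|
| 1.00 | 5.0% | 3.7% |
| 1.05 | 5.6% | 4.0–4.1% |
| 1.10 | 6.2% | 4.4% |

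**6. Power when clustering is respected.** At DEFF 1.1, power is 80.0% with 68 583 births and 79.7% with 68 000. Ignoring clustering, it would appear as 83.6% and 83.3%.

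**The case against.** There are four fair points on the other side.

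- **Crude may mean only that no covariates are adjusted for.** The word does not fix the variance estimator. The next sentence shows that the authors have within-woman clustering of these same two outcomes in mind, and arm might be a term in the GEE models. This stands as a possible reading, but the text neither gives the risk ratio a clustered variance nor says that arm is in the GEE. The ambiguity is itself a reason for a sentence of clarification.
- **A condensed article may leave the variance to the SAP.** True of silence in general. Here, however, the article names an estimator for its randomised objective and names the clustering remedy for another analysis, so the mismatch is in what is stated.
- **The pooled random-effects result is protected.** A reader might infer that the primary pooled test runs at 6.2%. The documents do not support that: the plan names random-effects pooling, and under the assumed estimator in the working the error stays below 5% at DEFF 1.1. This objection stands in full. It does not rescue the site-specific intervals, and an error rate held because clustering is mistaken for heterogeneity is not a good basis for the interval.
- **The effect is small.** This also stands. A reader might extend the range to DEFF 1.2, where the type I error would be 7.4%, but with two births per woman that needs rho = 0.2, outside the plan's own assumptions of at most two births and rho below 0.1.

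**Conclusion.** The point holds in limited form. The stated analysis of the randomised contrast does not match the unit of randomisation or the basis of the sample size. At the plan's ceiling DEFF of 1.1, the correct site-specific, simple pooled or fixed-effect interval is about 5% wider than the crude one. The type I error lies between about 5.05% and 6.2% over the range examined. In the random-effects analysis the consequence is overstated heterogeneity rather than a demonstrated excess of false positives.

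This rests on reading the crude ratio as having its ordinary birth-level interval, on 1:1 allocation and two-sided testing, and on assumed lower values for births per woman and rho. The 4.4% for random effects further assumes DerSimonian-Laird pooling and no true heterogeneity. The design effect is given for stillbirths only. The same mechanism applies to NMR, but the article gives no correlation from which to size it.

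Nothing here biases the risk ratio, and at the planned effect the interval moves only in the third decimal place. Severity: minor to moderate.

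**What to change.** State under Objective 1 that the FBH+ versus FPH risk ratios for SBR and NMR, by site and pooled, will come from a log-link GEE with arm (and site when pooled), clustered on woman, or otherwise with standard errors clustered on woman. Add that these woman-clustered log risk ratios and standard errors are the inputs to the random-effects meta-analysis. Crude ratios can remain as description.

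The cost is one sentence. GEE is already planned and no further data are needed. Intervals become up to about 5% wider, and the factor of 1.1 in the sample size already covers this.
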